*This document was originally submitted in German to the responsible ethics committee and was subsequently translated into English. [name] got married and is now named [name].*

Title of the study: Further development of the computer-based training program "Restart" for individuals with gambling problems: A randomized controlled trial

Lead investigator: [name] [name]

[contact]

University Medical Center Hamburg-Eppendorf

Center for Psychosocial Medicine

Clinical Neuropsychology Working Group

[name]

[name]

Cooperation partner: [name]. [name]

[contact]

University Medical Center Hamburg-Eppendorf

Center for Psychosocial Medicine

Clinical Neuropsychology Working Group

[name]

[name]

Funding: No

Planned project period: April 2021 until April 2022

Background: According to a representative study of the 16- to 70-year-old population in Germany, 75.3% of respondents have participated in gambling at least once in their lives. The 12-month prevalence for problem gambling behavior is 0.39% and for pathological gambling behavior 0.34% (Banz, 2019). However, a high number of unreported cases is assumed here. The 12-month prevalence of sports betting in Germany was 2.2% in 2019 (Banz, 2019). Live sports betting on the internet is considered to have a high-risk potential (Meyer & Bachmann, 2017). Individuals with problematic or pathological gambling behavior are often very ashamed of their symptoms and have difficulty acknowledging them (Suurvali et al., 2012), which leads to reduced treatment uptake. Studies show that up to 90% of those affected do not seek treatment (Slutske et al., 2009). Internet-based interventions are one way of reducing the treatment gap for people with problematic and pathological gambling behavior (Bücker et al., 2019). These interventions are an effective alternative to conventional face-to-face interventions in the treatment of mental illness (Carlbring et al., 2018).

Objectives: The main objective of this study is to investigate the online program "Restart" (online self-help program for people with problematic gambling or gambling disorder) regarding its effectiveness, acceptance and participants' motivation for treatment. The basis is the version of the online program used in the preliminary study (Bücker, Westermann, Kuhn & Moritz, 2019; Bücker et al., under review) and the findings gained from it. In addition to an introductory module, the initial version of "Restart" included 10 further modules designed to help users overcome emotional and gambling-related problems. These are dedicated to the topics of "mindfulness", "positive activities", "sleep", "self-worth", "changing your thinking", "ABC scheme", "social skills", "dealing with gambling urges", "debt regulation" and "preventing relapses". In the new version to be examined, the online program was expanded to include a module on sports betting, an interactive module for building motivation (which

appears immediately after the first login to the program), reminders in the form of e-mails to increase adherence (twice a week) and a new layout (modernization of the user interface). A new smartphone app that can be used in combination is also offered.

Procedure: The planned study will be conducted as a randomized controlled trial. It is a two-arm study consisting of an intervention group, which will have access to the online program for 6 weeks after the baseline surveys, and a waitlist control group, which will have access to the intervention following the post-assessment. The baseline and post-surveys will assess socio-demographic and psychopathological and will be conducted online and anonymously via Questback®. The following instruments will be assessed: Sociodemographic data, Pathological Gambling Y-BOCS (PG-YBOCS), Patient Health Questionnaire PHQ-9), South Oaks Gambling Scale (SOGS), Gambling Attitudes and Beliefs Scale (GABS), Attitude Towards Psychological Online Interventions Questionnaire (APOI), Patient Questionnaire for Therapy Expectation and Evaluation (PATHEV), Positive and Negative Effects of Psychotherapy Scale for internet-based Interventions (PANEPS-I) and a questionnaire to record the subjective evaluation of the training (ZUF-8).

Online forums dealing with problematic gambling will be used for recruitment. In addition, a Google AdWords/Facebook campaign will be launched. Inclusion criteria for the study are age between 18 and 70 years, informed consent, internet access, sufficient command of the German language, willingness to participate in two anonymous online assessments each lasting approx. 25-30 minutes, willingness to participate in a 6-week online program, willingness to use the program at their own risk, presence of gambling symptoms, presence of a desire for treatment, and willingness to leave an e-mail address and receive e-mails twice a week. For the latter, instructions for creating a free and anonymous e-mail address are

provided. The presence of lifetime schizophrenic or bipolar disorder or acute suicidal tendencies are exclusion criteria.

Statistical analysis plan: The results will be analyzed using an intention-to-treat analysis (ITT) and a per-protocol analysis (PP). Missing values in the ITT will be checked using both LOCF (last observation carried forward) and multiple imputations (MI). An analysis of covariance (ANCOVA) with baseline values as covariates is used as the primary statistical analysis. The sample size calculation was performed with G\*Power and resulted in a sample size of 199 subjects based on a small to medium effect size  $f=0.20$  (based on the results obtained in the previous study), a power of .80 and an  $\alpha=.05$ . Considering an expected dropout rate of 20%, this results in a total sample size of 238 subjects.

Expected benefit: We expect a greater reduction in gambling symptoms in the intervention group compared to the wait-list control group. By modifying and optimizing the program, we expect that the effects of the first efficacy study can be increased (Bücker et al., under review). The Restart online program is constantly being improved and adapted to the needs of the target group. The study will also gain knowledge about attitudes towards online self-help programs among those affected by problematic gambling or gambling disorder and their motivation for treatment. Side effects were not assessed in previous, similar studies.

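### With one baseline and one post survey, LOCF imputes zero change for every dropout; it should not stand unranked beside MI as a way of handling missing ITT values

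*Protocol*

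**What the plan says.** Under its statistical analysis plan heading, the protocol announces an intention-to-treat and a per-protocol analysis and then states: "Missing values in the ITT will be checked using both LOCF (last observation carried forward) and multiple imputations (MI"). Neither method is called primary or sensitivity. The model is fixed: "An analysis of covariance (ANCOVA) with baseline values as covariates is used as the primary statistical analysis".

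The number of assessments follows from two places. The inclusion criteria ask for "willingness to participate in two anonymous online assessments each lasting approx. 25-30 minutes", and the Procedure section names only a baseline and a post survey. No interim survey is described. The comparator is "a waitlist control group, which will have access to the intervention following the post-assessment".

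The sample size calculation uses f=0.20, power .80 and alpha .05, and "resulted in a sample size of 199 subjects". An expected dropout of 20% brings the total to 238. Dropout is not split by arm, and no expected change on the waitlist is given.

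**The concern.** LOCF needs a series of visits to carry anything other than baseline. Here there is one follow-up, so it amounts to carrying baseline forward: each missing post score is replaced by the participant's own baseline score, and the ANCOVA treats that value as an observation.

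Zero change is a strong assumption in this trial. Entry requires gambling symptoms and a desire for treatment, so some improvement without the program (regression to the mean, help-seeking) is plausible. The protocol's own hypothesis of a greater reduction under the program rules out zero mean change in both arms.

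The reasons for missing the post survey may also differ by arm. Waitlist participants get access after the post survey and so have an incentive to complete it; intervention participants have already had their six weeks. At stake are the size of the reported effect, the power and, in some circumstances, the type I error of an ITT result that the plan allows to be reported.

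**Working it through.** **Inputs from the protocol:** two assessments; ANCOVA adjusted for baseline; f=0.20; alpha .05; power .80; 199 before and 238 after the dropout allowance; 20% dropout overall.

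**Inputs assumed, not in the protocol:** equal allocation (119 per arm); f taken on the baseline-adjusted scale; baseline and post SD of 1; pre-post correlation 0.5; waitlist mean change c0 between 0 and -0.5 SD; arm-specific dropout averaging 20%; dropout unrelated to outcome within arm.

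**The plan's own figure.** Noncentral F with 1 and N-3 degrees of freedom and noncentrality f²N: N=199 gives power 0.802, so 199 is reproduced. With 238 randomised and 20% lost, about 190 remain (238 × 0.80 = 190.4) and power is 0.78. That is the benchmark for completers below.

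**True effect on the score scale.** For two equal groups d = 2f = 0.40 residual SD. The residual SD is √(1-0.5²) = 0.866, so the effect is 0.40 × 0.866 = 0.346 baseline SD, written -0.346 because lower scores are better.

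**What LOCF estimates.** Let d1, d0 be the dropout and c1, c0 the true mean change in the intervention and control arms. A fraction d of each arm is given zero change, so the expected group difference is

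(1-d1)·c1 - (1-d0)·c0, with c1 = c0 - 0.346 if the program works.

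- 20%/20%: 0.8 × (-0.346) = -0.277 whatever c0 is, a 20% attenuation.
- 30%/10% (intervention/control): 0.7(c0 - 0.346) - 0.9·c0 = -0.242 - 0.2·c0. This is -0.24 at c0 = 0 and -0.14 at c0 = -0.5.
- 10%/30%: 0.9(c0 - 0.346) - 0.7·c0 = -0.311 + 0.2·c0. This is -0.31 at c0 = 0 and -0.41 at c0 = -0.5. It exceeds the true effect in size only if 0.2·c0 < -0.035, that is, if the waitlist improves by more than about 0.17 SD.
- No true effect (c1 = c0 = c): c(d0 - d1). This is zero if dropout is equal or if there is no common change.

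**Simulation.** ANCOVA of post on arm and baseline, 3,000 to 10,000 trials per scenario. The mean estimates matched the formula. Power and rejection rates from separate runs agreed to within about two percentage points.

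| Dropout int./control | Common improvement | LOCF estimate | LOCF power | Completer ANCOVA power |
|---|---|---|---|---|
| 20%/20% | 0 | -0.28 | 76% | 78% |
| 20%/20% | 0.5 SD | -0.28 | 71% | 78% |
| 25%/15% | 0 | -0.26 | 70% | 78% |
| 25%/15% | 0.5 SD | -0.21 | 47% | 78% |
| 30%/10% | 0 | -0.24 | 63% | 77% |
| 30%/10% | 0.5 SD | -0.14 | 25% | 77% |
| 10%/30% | 0 | -0.31 | 85% | 78% |
| 10%/30% | 0.5 SD | -0.41 | 96% | 78% |

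With no true effect, LOCF rejects in about 5% of trials when there is no common change, whatever the dropout. With 0.5 SD common improvement it rejects in about 7.5% at a 10-point gap and 15% at a 20-point gap, against the program if its arm loses more and in its favour if the waitlist does. Completer ANCOVA stays near -0.35 with a true effect and at about 5% without one.

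Varying the pre-post correlation from 0.3 to 0.7 at 30%/10% and 0.5 SD gives LOCF power of 19 to 27% and null rejection of 13 to 21%.

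MI itself was not simulated. Completer ANCOVA stands in for it, since the two should agree closely under this dropout mechanism.

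**The case against.** **The two methods are not declared equal.** A reader might infer that LOCF has the same standing as MI. The text does not say so. It says that missing values will be checked with both, which in a translated document may mean no more than a cross-check, and a separate SAP might rank them. That stands, so the point cannot rest on the missing ranking alone. It rests on the protocol naming a method that, in this design, can only impute zero change.

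**The direction is not fixed.** A reader might infer that higher control dropout always flatters the program. It does not: at 10%/30% with no waitlist improvement the effect is still understated. The opposite inference, that LOCF is safely conservative, fails once the waitlist improves by more than about 0.17 SD.

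**Unequal dropout is conjecture.** The waitlist incentive is an inference, and the twice-weekly e-mail reminders in the new program version may keep intervention participants engaged. The protocol gives only an overall rate. This stands: the severe figures need both a large gap and a sizeable common improvement, and neither is documented.

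**The comparison favours MI by construction.** Dropout was generated unrelated to outcome within arm. If dropouts truly improve less than completers, standard MI is biased too and no change may be nearer the truth. This also stands. It argues for keeping a no-change scenario as a labelled sensitivity analysis, not for leaving it unranked.

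**Conclusion.** The concern holds in conditional form. That LOCF sets every dropout's change to zero follows from the two-survey design and needs no assumption. With a real effect, no waitlist change and equal 20% dropout, that alone shrinks the estimate by a fifth and costs a few points of power (about 76% against 78%).

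Anything worse depends on two things the protocol does not give: how far dropout differs between arms, and how much the waitlist improves. Over the range shown, power at 30%/10% dropout falls to 63% or 25%, the effect can be understated or overstated, and the false-positive rate runs from nominal to 15%. The documents do not support a claim that the trial will be biased by any particular one of these amounts, or in a known direction. A valid approach under missingness at random is already planned, so this is a correction worth making rather than a fatal flaw.

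**What to change.** State that multiple imputation is the single primary handling of missing post scores in the ITT analysis, imputed separately by arm. Use baseline PG-YBOCS and the other measures actually taken at baseline as predictors. The Procedure section lists the instruments for both surveys together, so which ones are available at baseline (APOI and PATHEV, for example) must be confirmed first.

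Delete LOCF, or keep it only as a sensitivity analysis labelled as a no-change scenario for dropouts. A delta-adjusted MI can serve as the sensitivity analysis for data not missing at random. Report dropout by arm so that readers can judge how much the choice matters.

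The cost is a few sentences in the protocol or SAP and a little analysis work. No extra data or participants are needed, and MI is already planned.

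### The 20% dropout allowance is multiplied on (199 × 1.2) instead of divided out (199 / 0.80), so 238 enrolled leaves about 190 with post-assessment data, 9 short of the plan's own 199

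*Protocol*

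**What the plan says.** The sample size is in the Statistical analysis plan paragraph of the protocol. The primary method is fixed there: "An analysis of covariance (ANCOVA) with baseline values as covariates is used as the primary statistical analysis". The G*Power calculation "resulted in a sample size of 199 subjects based on a small to medium effect size", namely f = 0.20, with power .80 and alpha .05. The next sentence makes the dropout allowance: "Considering an expected dropout rate of 20%, this results in a total sample size of 238 subjects".

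Two other statements bear on what these numbers mean. The Procedure paragraph describes the design: "It is a two-arm study consisting of an intervention group" and a waitlist control group, with surveys at baseline and post only. The statistical paragraph plans both an intention-to-treat and a per-protocol analysis, and says of the former: "Missing values in the ITT will be checked using both LOCF (last observation carried forward) and multiple imputations (MI". The protocol gives no other dropout rate and no other inflation formula.

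**The concern.** A dropout rate is ordinarily the fraction of enrolled participants who are lost. To end with a required number, that number is divided by the fraction retained. Adding the same percentage to the required number always gives too few, because the loss then applies to the larger total.

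The 238 looks like the second operation. If so, three figures in two adjacent sentences (238 enrolled, 20% lost, power .80 from 199) are mutually inconsistent. A reader who later compares recruitment and retention with the plan would take 238 enrolled with 20% dropout as meeting the design, when by the plan's own calculation it falls short.

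**Working it through.** **Inputs.** From the protocol: f = 0.20, alpha = .05, power = .80, two arms, ANCOVA with baseline as covariate, N = 199 before dropout, dropout 20%, N = 238 after. Assumed: equal groups and the usual F test (two-sided in effect), since the protocol states neither allocation ratio nor sidedness.

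**Step 1: reproduce 199.** Noncentral F test with 1 and N − 3 degrees of freedom (two groups, one covariate) and noncentrality f² × N = 0.04 × N.

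| N | Power at f = 0.20 |
|---|---|
| 190 | 0.783 |
| 198 | 0.7997 |
| 199 | 0.8017 |
| 238 | 0.867 |

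The smallest N reaching .80 is 199, an exact match. Zero or two covariates give the same N. A one-sided test would need only 156, so the two-sided convention is the one that fits the protocol's figure.

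**Step 2: find the origin of 238.**
- Multiplying: 199 × 1.2 = 238.8. The stated 238 is this value rounded down; rounding up would give 239.
- Dividing: 199 / (1 − 0.20) = 248.75, so 249.

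Only the first comes near the stated figure. The second is what a 20% loss of enrolled participants requires. The gap is 249 − 238 = 11, and 11 / 249 = 4.4% of the required enrolment.

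**Step 3: what 238 delivers at 20% dropout.** 238 × 0.80 = 190.4, so about 190 with a post-assessment, and 199 − 190 = 9 short. ANCOVA power on those 190 is 0.783 (0.784 at 190.4).

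**Step 4: the dropout rate that 238 can absorb.** 1 − 199 / 238 = 39 / 238 = 16.4%.

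**Step 5: dependence on assumptions.** Steps 2 and 4, and the head count in step 3, use only 199, 20% and 238. Only the power figures use equal groups and the F-test convention.

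**The case against.** **The intention-to-treat analysis uses everyone.** With LOCF and multiple imputation, all 238 are analysed, so it could be said that nobody is lost. Part of this stands: 190 is the expected number with observed post-assessment data, not the size of the intention-to-treat set, and 78% is the power of a complete-case ANCOVA. It does not rescue the 238. The 0.867 at N = 238 would need an observed outcome for every participant. Imputation does not in general restore the missing outcome information, and with only two assessments LOCF carries the baseline value forward. If imputation did make up for dropout, 199 would suffice and no allowance would be needed; the protocol chose to make one.

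**The 20% may be a reserve on top of 199.** The text calls it an expected dropout rate, which does not read that way. Even so, the reserve would imply 0.2 / 1.2 = 16.7% of those enrolled, and 238.8 would still round up to 239.

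**The effect is negligible.** This largely stands as to size. The effect detectable with .80 power at 190.4 is about f = 0.204 rather than 0.20, a shift smaller than the precision to which f is given.

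**Stronger readings.** A reader might infer that the trial is materially underpowered, or that the planned primary analysis has 78.3% power. The document supports neither. The loss is 0.802 − 0.783 = 0.019, or about 1.7 points below the nominal .80. The power of the LOCF or multiple-imputation analysis depends on the dropout mechanism and the baseline–post correlation, which the protocol does not give.

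**Conclusion.** The point holds as a minor but definite error in a stated design figure. The base of 199 is right; the inflation step is wrong. At the plan's own 20% dropout, 238 enrolled leaves about 190 with post-assessment data, and complete-case ANCOVA power at f = 0.20 is about 78%, not 80%. The size, dropout rate and power as written cannot all be true together.

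The inconsistency follows from the protocol's own three numbers, reading the dropout rate as a share of those enrolled. The power figure further assumes equal groups, the conventional F test and analysis of participants with observed post data. The estimand, analysis method and error rate are untouched. A reader might also infer that recruitment has to rise to 249. It does not: that is the number consistent with 199 and 20%, but a correct statement of what 238 delivers removes the error just as well.

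**What to change.** Keep 238 and replace the dropout sentence with one to this effect: *With 238 participants enrolled and 20% dropout, about 190 are expected to have post-assessment data, giving about 78% power at f = 0.20 in those with post data; power of .80 holds if dropout does not exceed about 16%.*

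Referring to participants with post-assessment data, rather than evaluable participants, keeps the sentence consistent with the intention-to-treat text in the same paragraph. The cost is one sentence, with no change to recruitment, assessments or analysis.
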